##### Distress Thermometer for Parents

The Distress Thermometer for Parents [48] consists of 3 sections examining parent distress levels and specific problems over the previous week. Parents indicate their distress on a thermometer scale ranging from 0 (*no distress*) to 10 (*extreme distress*); a score of 4 or higher is indicative of clinically elevated distress. They also complete a 34-item problem list spanning 6 domains: practical, social, emotional, physical, cognitive, and parenting. Finally, questions regarding perceived support and understanding from others, parental chronic disease, relationships with medical staff, and desire to consult a health professional about the situation are completed. The Distress Thermometer for Parents has been validated as a short screening tool for identifying parental distress [48].

##### McMaster Family Assessment Device

The McMaster Family Assessment Device [49] is based on the McMaster model of family functioning and contains statements concerning the family’s functioning. The measure requires respondents to indicate their level of agreement with each statement on a 4-point Likert scale *(*strongly agree to strongly disagree). Higher scores indicate poorer family functioning. For this study, only the General Family Functioning Scale will be used (12 items), and it has been shown to have good reliability and validity [50].

### Implementation Measures

Table 3 summarizes the implementation measures mapped according to the RE-AIM framework. These measures evaluate implementation processes and any factors (barriers and enablers) influencing implementation of the EMERGE model of care.

**Table 3. T3:** Implementation measures using the RE-AIM^a^ framework.

Implementation outcome and tool	Source	Phase
Reach		
Percentage uptake among eligible families		
Recruitment log	Trial database	End of trial
Representativeness of participants for Victorian ALL^b^ population		
Recruitment log	Trial database	End of trial
Acceptability of model		
Experience of Care survey	Consumers	Evaluation 1^c^ Evaluation 2^d^
Semistructured interviews (subset)	Consumers HCPs^e^	Evaluation 2
Acceptability of the telehealth platform		
Experience of care survey	Consumers	Evaluation 1 Evaluation 2
Semistructured interviews (subset)	Consumers HCPs	Evaluation 2 12 months
Effectiveness		
Information needs		
Information Needs survey	Consumers	Screening Evaluation 1 Evaluation 2
Satisfaction with intervention		
Client Satisfaction Questionnaire	Consumers	Evaluation 1 Evaluation 2
Experience of care		
Experience of Care survey	Consumers	Evaluation 1 Evaluation 2
Semistructured interview (subset)	Consumers	Evaluation 2
Health service usage		
Health services usage log	Consumers	Evaluation 2
Adoption		
Participation rates		
Recruitment log	Trial database	End of trial
Number of staff trained in EMERGE administration		
Training Log	Trial database	End of trial
Implementation		
Percent of survivorship care plans provided		
Care plan log	Trial database	End of trial
Adherence		
Referral log	Trial database	End of trial
Recommendations log	Trial database	End of trial
Percent of participants who completed 2 telehealth sessions		
Telehealth session log	Trial database	End of trial
Percent of participants who received an information resources pack		
Resource allocation log	Trial database	End of trial
Acceptability, appropriateness, and feasibility of the intervention		
Acceptability Intervention Measure, Intervention Appropriateness Measure, and Feasibility of the Intervention Measure	HCPs	Baseline^f^ 12‐24 months
Maintenance		
Staff undertaking procedures		
Telehealth session log	Trial database	Evaluation 1 Evaluation 2
Follow-up work log	Trial database	Evaluation 1 Evaluation 2
Length of consultation		
Telehealth session log	Trial database	Evaluation 1 Evaluation 2
Time spent on follow-up		
Follow-up work log	Trial database	Evaluation 1 Evaluation 2
Sustainability of EMERGE model		
Health Economics Evaluation		
CHU9D^g^ and AQoL-4D^h^	Consumers	Screening^i^ Evaluation 2 12 months
MBS^j^ and PBS^k^ data	Services Australia	24 months
Cost of model integration into service	Trial database	Evaluation 2
HCP and institutional evaluation		
Semistructured interviews	HCPs	12‐24 months
Semistructured interviews	Executive staff	End of trial

a RE-AIM: Reach, Effectiveness, Adoption, Implementation, and Maintenance.

b ALL: acute lymphoblastic leukemia.

c Evaluation 1: following consultation 1.

d Evaluation 2: following consultation 2.

e HCP: health care provider.

f Baseline: beginning of trial implementation.

g CHU9D: Child Health Utility 9D.

h AQoL-4D: Australian Quality of Life Instrument.

i Screening: before consultation 1.

j MBS: Medicare Benefits Scheme.

k PBS: Pharmaceutical Benefits Scheme.

#### Acceptability of Intervention Measure, Intervention Appropriateness Measure, and Feasibility of Intervention Measure

The Acceptability of Intervention Measure, Intervention Appropriateness Measure, and Feasibility of Intervention Measure [51] are 3 implementation measures designed to measure the degree of fit or match of something to a desired criterion and allow for evaluating the success of the implementation efforts. These measures specifically assess the acceptability, appropriateness, and feasibility of the intervention. Responses are made on a 5-point ordinal scale ranging from “*completely disagree*” to “completely agree.” Each of the measures has been shown to have good reliability (Acceptability of Intervention Measure Cronbach α=0.85, Intervention Appropriateness Measure Cronbach α=0.89, and Feasibility of Intervention Measure Cronbach α=0.89) as well as good conceptual validity [51]. These measures will be completed by the health care provider before and after the implementation of the EMERGE intervention.

#### Semistructured Interviews

A subset of parents (n=20, 25%) and health care providers (n=10‐15) from the RCH and (n=5‐10) from MCH will be asked to complete a semistructured interview (with a researcher not involved in delivering the program), 12‐24 months following the EMERGE intervention being active at their site. Interviews will include questions related to the acceptability of the EMERGE model, experience of care, barriers and facilitators to the delivery, and sustainability of the EMERGE model.

### Outcome Measures

#### Information Needs Survey

An information needs survey has been developed for this study and was adapted from an original survey used in the Adolescent and Young Adult Health Outcomes and Patient Experience (AYA Hope) study [52] and a subsequent Australian study of adolescent and young adult cancer survivors [53]. Parent participants and adolescent participants older than 16 years will be asked to rate their need for more information on items such as their treatment side effects, cancer relapse, physical functioning, survivorship plan, and community-based services. Participants respond to each of the 31 items, indicating (1) *I have enough information*, (2) *I need some more information*, (3) *I need much more information*, and (4) *does not apply*.

#### National Institutes of Health Toolbox Perceived Stress Scale

The National Institutes of Health Toolbox Perceived Stress Scale [54] is a self-report measure of an individual’s perceptions about the nature of events and their relationship to the values and coping resources of an individual. This is a 10-item measure, rated on a 5-point Likert scale (0*=never* to 4*=very often*). It assesses how unpredictable, uncontrollable, and overloaded respondents find their lives. The perceived stress module is normed from 18 to 85 years of age and provides a *t* score with a mean of 50 (SD 10). The Perceived Stress Scale has demonstrated good reliability (Cronbach α=0.91) and content validity [54].

#### The Client Satisfaction Questionnaire

The Client Satisfaction Questionnaire [55] is a self-report measure of satisfaction with services received by individuals and families in the health and human services settings. The measure has 8 items that target: quality of service, kind of service, met needs, recommend to a friend, amount of help, deal with problems, overall satisfaction, and return intent. Responses are made on a 4-point Likert scale, with high scores indicating higher satisfaction. Reliability and validity testing in health care contexts support good reliability (Cronbach α=0.83-0.93) and validity [55].

#### Experience of Care Survey

This survey has been developed specifically for the EMERGE study and adapted from other health intervention implementation studies. The survey comprises 7 questions which parents respond to on a 5-point Likert-type scale ranging from strongly agree to strongly disagree. Example items include “*I was able to ask all the questions I had about my child*,” “*There was enough time to cover all the areas I wanted to discuss during the session*,” and “*The telehealth platform was easy to use*.”

### Health Service Usage

#### Medicare Benefits Schedule Data and Psychosocial Service Usage

To capture health service usage during the period of intervention, we will obtain consent (optional) to access the patient’s Medicare Benefits Schedule data via Services Australia. This consent will be sought by the research team to align with the family’s second telehealth session. The data will provide information relating to Medicare Benefits Schedule–billed medical visits and procedures, and the associated costs (eg, general practitioners, diagnostics, and specialists, including psychosocial services where Medicare is subsidized). Data will be requested for a 24-month period post-treatment.

##### Child Health Utility 9D

The Child Health Utility 9D (CHU9D) [56] is a preference-based measure of health-related QoL for children and adolescents. Parent-proxy forms will also be used to monitor patient QoL in this study. The questionnaire assesses 9 dimensions—worries, sadness, pain, tiredness, annoyance, schoolwork, sleep, daily routine, and activities. Responses are made on a 5-point ordinal scale of “*no*” to “very.” The CHU9D consists of a descriptive system and a set of preference weights, giving utility values for each health state described by the descriptive system, allowing the calculation of quality adjusted life years (QALYs). The measure has been shown to have good reliability [57] and construct validity [58].

##### The Australian Quality of Life Instrument

The Australian Quality of Life Instrument (AQoL-4D) [59] is a multiattribute utility health-related QoL instrument, which will be used to monitor parent QoL in this study. The AQoL-4D consists of 12 items assessing 5 dimensions: illness, independent living, social relationships, physical senses, and psychological well-being. Each item has 4 response levels. The AQoL-4D uses a descriptive system and set of preference weights that provide utility values for each health state described by the descriptive system. As with the CHU9D, this will allow for the calculation of QALYs [59].

### Data Analysis

#### Sample Size Estimation

The RCH and MCH collectively treat approximately 90 children and adolescents annually who are diagnosed with ALL. Given that approximately 15% (n=9) of these patients may relapse, become palliative, or die, and recruitment will occur over a 24 to 30-month period, we anticipate recruitment of approximately 100 families over the course of the project (allowing for some families opting not to participate and some withdrawals due to disease recurrence).

#### Data Analysis Plan

Feasibility and acceptability of the EMERGE model will be assessed by calculating recruitment and participation rates, acceptability ratings by clinical staff, and parents’ or patients’ satisfaction measured post-intervention (eg, length, content, and information). Descriptive statistics will be used to report sample characteristics and for all quantitative measures. Intention to treat will be used to analyze primary outcome measures (satisfaction, information needs, and parent stress ratings). Change between time points in information needs and stress ratings will be analyzed using paired *t* tests. In order to detect a clinically meaningful change from baseline of 0.3 of an SD, with 80% power and error rate α=.05, a sample size of n=100 is required. Univariate and multivariate analyses will be used to identify psychosocial, demographic, and treatment-related variables associated with parent information needs and stress ratings. With a sample of n=100 (80% power, α=.05), we will be powered to detect a medium size of effect (*f*^2^=0.15) in multiple linear regression models with up to 5 predictors. Secondary outcomes such as uptake or adherence to recommendations will be calculated (frequencies and percentages).

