Sleep issues	Parent proxy Child^b^	Screening Monitoring	PROMIS Sleep-related disturbance (4-item) and PROMIS Sleep-related impairment (4-item)
Meaning and purpose	Parent proxy Child^b^	Screening Monitoring	PROMIS Meaning and Purpose (4-item)
Friendships	Parent proxy Child^b^	Screening Monitoring	NIH^e^ Toolbox Friendship (5-item)
Social relations	Parent proxy Child^b^	Screening Monitoring	Neuro-QOL^f^ Pediatric Social Relations – interactions with peers (8-item)
Parent assessment			
Stress	Parent	Screening Evaluation 1^g^ Evaluation 2^h^	NIH Toolbox perceived stress module (10 items)
Distress	Parent	Screening Monitoring	Distress Thermometer for Parents (single item plus 34 item problem list)
Family assessment			
Family functioning	Parent	Screening	McMaster Family Assessment Device (12 items)

a Screening: before consultation 1.

b Child aged more than 8 y.

c Monitoring: before consultation 2.

d PROMIS: Patient-reported Outcomes Measurement Information System.

e NIH: National Institutes of Health.

f Neuro-QOL: Quality of Life in Neurological Disorders.

g Evaluation 1: following consultation 1.

h Evaluation 2: following consultation 2.

Fourth, psychoeducation or resource provision: psychoeducation and counseling will be provided directly by the EMERGE advanced practice nurse and psychosocial clinician during the 2 scheduled telehealth sessions. Telehealth sessions will occur at least 3 months apart for families with a minimum of 2 consultations. Information resources will be provided both electronically and in hard copy if required and will directly address concerns identified in each of the EMERGE telehealth sessions (eg, immunization schedule, sleep, when to call the hospital, fatigue, financial resources, and cancer charities).

Fifth, documentation: a summary letter, personally addressed to the parent and, if applicable, adolescent, will be provided both electronically and in hard copy to families after each EMERGE consultation, along with the treatment summary, roadmap, and information resources. With parent permission, these documents will also be shared with the child’s general practitioner or pediatrician. Documents will also be sent to the primary oncologist and uploaded into the patient’s electronic medical record.

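### Intention to treat is promised for information needs and parent stress, but the paired t tests named use only complete pairs, and the main follow-up is not fixed

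*Protocol article*

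**What the plan says.** The Data Analysis Plan states that "Intention to treat will be used to analyze primary outcome measures" and lists three: satisfaction, information needs and parent stress. The next sentence fixes the test: "Change between time points in information needs and stress ratings will be analyzed using paired" t tests. The power statement that follows is based on a "clinically meaningful change from baseline of 0.3 of an SD" and concludes "with 80% power and error rate α=.05, a sample size of n=100 is required".

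Both change outcomes are measured three times. Table 2 schedules the parent stress scale at "Screening Evaluation 1^g^ Evaluation 2^h", and Table 3 schedules the information needs survey at "Screening Evaluation 1 Evaluation 2". The table footnotes place Screening before consultation 1, Evaluation 1 after consultation 1 and Evaluation 2 after consultation 2. Table 3 schedules the satisfaction questionnaire at the two evaluations only, so it has no baseline.

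Incomplete follow-up is foreseen. Sample Size Estimation allows for "some withdrawals due to disease recurrence", and Table 3 makes the percentage of participants completing both telehealth sessions an outcome in its own right. The article gives no loss rate for the paired tests and no means of keeping incomplete families in them.

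Study Aims places these same outcomes under the secondary aim, although the Data Analysis Plan calls them primary.

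**The concern.** The stated principle and the stated test do not match. Intention to treat is meant to stop attendance from deciding who is analysed. A paired t test on observed data lets it decide: a family without consultation 2 has, on the published schedule, no Evaluation 2 score and so no pair for that contrast. Families who stop attending may differ in baseline stress or information need, and change depends on baseline. If they differ, the mean change among completers is not the mean change among those enrolled.

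The second gap is the contrast. With two follow-ups and no main one named, it can be chosen after the results are known, and each extra test at .05 adds a chance of a false positive.

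**Working it through.** **The plan's own figure.** A paired t test at d = 0.3 (in SDs of the change), two-sided .05 (sidedness is assumed) and 80% power needs 90 complete pairs by the noncentral t. The normal approximation gives ((1.96 + 0.84)/0.3)², or 88 after rounding up. At n = 100 the power is 84.4%. The stated 100 is matched by 90/(1 − 0.10) = 100, but the article states no 10% loss. The point does not depend on this difference.

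**Who is in each test.** Loss is per contrast:
- Evaluation 1 missing only: the family stays in Screening to Evaluation 2.
- Evaluation 2 missing only: it stays in Screening to Evaluation 1 and leaves Screening to Evaluation 2.
- Both evaluations missing: it leaves both.

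**Size of the completer bias.** Assume equal variances, pre-post correlation r, and dropout that depends on the baseline score only. In SD units, expected change given baseline X is δ − (1 − r)(X − μ). If a fraction p is lost and the lost families start D above the completers, the completers' baseline mean is μ − pD. Their mean change is therefore δ + (1 − r)pD, and the bias is p × (1 − r) × D.

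The documents give none of p, r or D, so all three are assumptions:

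| Loss p | r | Gap D (SD) | Bias (SD) | Share of 0.3 SD |
|---|---|---|---|---|
| 10% | 0.5 | 0.3 | 0.015 | 5% |
| 20% | 0.5 | 0.3 | 0.03 | 10% |
| 20% | 0.5 | 0.5 | 0.05 | 17% |
| 20% | 0.5 | 1.0 | 0.10 | 33% |
| 20% | 0.7 | 1.0 | 0.06 | 20% |
| 20% | 0.3 | 1.0 | 0.14 | 47% |

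The sign follows D. With a true change of −0.30 SD, 20% loss and r = 0.5, completers show −0.20 if those lost start 1 SD higher and −0.40 if they start 1 SD lower. Simulation with logistic dropout on baseline agrees: −0.198 at a gap of +1.04 SD and −0.389 at −0.86 SD. An estimate that uses every family's baseline recovers −0.30 under this type of dropout.

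**Number of tests.** Change from baseline can end at Evaluation 1 or Evaluation 2, so there are 2 contrasts × 2 outcomes = 4 tests. If each is run at .05:
- Independent: 1 − 0.95⁴ = 18.5%.
- Simulated with assumed correlations of 0.5 between time points and 0.3 between outcomes: about 17%.
- One contrast per outcome, two independent tests: 1 − 0.95² = 9.75%.

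**The case against.** The strongest reply is that this is a journal article and the statistical analysis plan is not shown. Intention to treat can be read as defining the analysis set (all enrolled families, whatever they attended), and a paired t test can be run on imputed data. That stands in part. A reader might infer that paired t tests cannot deliver intention to treat. The documents do not support that, because imputation specified elsewhere would reconcile the two sentences. What remains is that the article commits to a principle and to a test that, as written, does not meet it.

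Three other stronger readings also fail:
- *Every family missing a follow-up is dropped.* Loss is per contrast, as shown above.
- *Six tests and a 26.5% false-positive risk (1 − 0.95⁶).* The words on change between time points would allow three contrasts per outcome. The power sentence, and the Costs and Consequences section, speak of change from baseline, which leaves out Evaluation 1 to Evaluation 2. The 26.5% also assumes independence, which contrasts sharing a time point do not have; six tests give about 22% under the correlations assumed above.
- *A bias of a third of the target effect.* At 20% loss and r = 0.5 this needs a baseline gap of about 0.9 to 1 SD, which is very large. The only cause of withdrawal that Sample Size Estimation names is disease recurrence, not parent stress.

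It is also fair to say that effectiveness is the secondary aim. The limitations section already urges caution and concedes that the pre-post design cannot exclude natural recovery or regression to the mean. It does not mention selective loss, and a different model would not cure the limitations it does admit.

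**Conclusion.** The point holds as a should-fix. Followed as written and without imputation, the analysis of information needs and parent stress is a complete-pair analysis for each contrast, despite the intention-to-treat label. The powered contrast is not identified beyond being from baseline.

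The bias may be small (0.03 SD for a 0.3 SD baseline gap) or material (0.10 SD for a 1 SD gap) at an assumed 20% loss and r = 0.5. Its direction is unknown. The 17% to 18.5% familywise error assumes that all four baseline contrasts are tested at .05; this is inferred from the absence of any ranking or adjustment and is not stated. The outcomes' place under the secondary aim of an uncontrolled design keeps the point below must-fix.

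**What to change.** 1. Replace the paired t tests with one linear mixed model per outcome, using all enrolled families with any measurement. Take time (Screening, Evaluation 1, Evaluation 2) as a fixed effect with unstructured covariance. Multiple imputation would also serve, provided it is stated.
2. Name Screening to Evaluation 2 as the main contrast for each outcome and make Evaluation 1 supportive.
3. Rank the two outcomes or split alpha, because two unadjusted tests still give 9.75%.
4. Report satisfaction as the number responding out of all enrolled, with their scores, and do not call it intention to treat.

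The model needs no new data and slightly more analysis work. It relies on scores being missing at random given those observed, so loss that depends on the unseen follow-up score would still bias it. Splitting alpha has a price: with the 81 families recruited, all pairs complete and d = 0.3, a paired test has 76% power at .05 and 66% at .025. Ranking spares the first outcome that loss. The Results section says data collection is ongoing and analysis is due in late 2026, so the change can still be made before analysis.

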#### Costs and Consequences

The assessment of costs will reflect the resources required for program delivery (as reflected by the type of practitioner involved in the delivery of the program and the time required) and the impact on subsequent health care service use (as reported from Medicare data and patient information for psychology services). Costs will be reported on the basis of total and average costs per patient for program delivery, subsequent health care use, and overall. Program consequences will be expressed in terms of the impact from baseline on unmet needs, satisfaction, and QALYs (as separate outcomes).

#### Qualitative Analysis

Health care provider and parent interviews will be analyzed deductively to code a priori themes related to implementation domains. Inductive analysis will also be used to identify novel or emerging data, using the thematic approach described by Braun and Clarke [60]. Deidentified interview transcripts will be imported into Lumivero NVivo software [61] for coding and analysis. Parent and health care provider interviews will be analyzed separately. Data analysis will examine differences between stakeholders and participants and across sites and will examine barriers and facilitators to the delivery of the EMERGE intervention.

